#### Comparative measurement in those smokers attending community stop smoking services

We will compare cessation rates at 4 weeks between the intervention and SBP groups with those smokers aged 55–80 attending the local stop smoking service over the same time period to delineate the effect of both SC interventions within YESS, using logistic regression and adjusting for observed baseline differences in predictors of cessation including age, gender, heaviness of smoking and level of education.

A detailed statistical analysis plan will be prepared prior to completion of trial recruitment, and agreed with the trial steering committee.

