### Blinding

The sequence of treatment allocations will be concealed until interventions have all been assigned and recruitment and data collection are complete. Once primary and secondary data from both treatment groups have been analysed by the trial statistician, the groups will be un-blinded to the Trial Management Group (TMG). Consent is taken at the 4-week visit by the SCP. In order to ensure concealment at the time of recruitment/consent, the personalised risk information booklet (further detail provided later) or a blank booklet are enclosed in a sealed envelope which is opened by the SCP following consent/data collection. This arrangement commenced five rounds into recruitment following review of processes at a Trial Steering Committee. For five rounds at the start of the trial, SCPs were aware of trial allocation at the time of consent/data collection. The impact of this will be assessed in a sensitivity analysis.

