### SC provision

#### All eligible smokers

Unless explicitly declined, all eligible YLST participants will attend a consultation with a specialist SCP, trained to National Centre for Smoking Cessation and Training standards,^31^ colocated within the screening van. Support will be provided in line with National Institute for Health and Care Excellence (NICE) PH48 guidance^32^ comprising one session of behavioural support at the time of the LHC and provision of pharmacotherapy (either as nicotine replacement therapy through delegated prescribing at the visit and/or a commercially available e-cigarette, or arrange a GP prescription for varenicline or bupropion). Follow-up contact either face-to-face or by telephone, typically weekly but more or less frequently according to participant preference for up to 4 weeks from the date of the LHC.

Where study SCP follow-up is not possible, or if the individual smoker prefers, contact details will be passed to the local NHSSSS for referral into community services immediately following the screening visit.

All eligible participants will be asked for consent to be contacted by telephone at 4 weeks, 3 months and 12 months after the screening visit solely to ascertain smoking status, with optional CO validation if quit. Approximately 4 weeks after the screening visit (and hence after scan results have been issued by YLST), the SCP will arrange a face-to-face visit with the smoker either at home or community location (according to the participant’s preference) to ascertain current smoking status (with CO validation in those reporting abstinence). Informed written consent for participation in the trial will be confirmed at this visit, and individuals treated according to their allocated group as follows:

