#### Secondary outcomes

Self-reported and CO validated continuous cessation at 4 weeks in all eligible smokers agreeing to receive SC from the SCP as part of the LHC.Self-reported continuous and seven day point prevalent SC at 3 months.Self-reported and CO validated continuous cessation at 12 months.Attempts to quit smoking.Changes in psychological variables, including perceived risk of lung cancer, motivation to quit smoking tobacco, confidence and efficacy beliefs (self and response) at all follow-up points.

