### Statistical analyses

We will compare baseline characteristics between randomised treatment groups descriptively. We will estimate the effect of the intervention by comparing our primary and secondary outcomes between intervention and SBP groups using logistic regression, presenting results in terms of the proportion achieving abstinence in the two groups, the risk difference and the OR, with 95% CIs.

Primary analysis will be on an intention to treat basis, assuming that missing data implies smoking, but we will conduct sensitivity analysis to examine the impact on our findings of alternative assumptions, including the Hedeker approach which assumes alternative relationships between having missing data and smoking, and using multiple imputation to test the alternative assumption that the data are missing at random (ie, missing data can be modelled using measured variables).

We do not plan a priori to adjust for any baseline covariate, presuming that randomisation will achieve balance between groups. We will look for effect modification of effect of intervention according to presence of absence of abnormal scan findings of emphysema or CAC, using the likelihood ratio test for interaction. In sensitivity analysis, we will analyse excluding those who were consented to the intervention group prior to change in timing of consent (n=94).

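### The 4-week measures precede the personalised booklet, so they cannot show its effect or separate the two YESS interventions against community services

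*Protocol article*

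**What the plan says.** Five parts of the protocol article bear on this.

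- **SC provision, All eligible smokers.** Every eligible smoker gets the same behavioural support and pharmacotherapy or e-cigarette, with contact "according to participant preference for up to 4 weeks from the date of the LHC". At a face-to-face visit about 4 weeks after screening the practitioner establishes smoking status. "Informed written consent for participation in the trial will be confirmed at this visit, and individuals treated according to their allocated group".
- **Blinding.** The personalised or blank booklet is "enclosed in a sealed envelope which is opened by the SCP following consent/data collection". This arrangement began five rounds into recruitment; before that, practitioners knew the allocation when they took consent and collected data.
- **Secondary outcomes.** The list opens with "Self-reported and CO validated continuous cessation at 4 weeks in all eligible smokers agreeing to receive SC". It also includes changes in psychological variables at every follow-up point, and 4 weeks is one of these.
- **Statistical analyses.** "We will estimate the effect of the intervention by comparing our primary and secondary outcomes between intervention and SBP groups using logistic regression". No time point is exempted.
- **Comparative measurement in those smokers attending community stop smoking services** (analysis part). Four-week cessation in the intervention and SBP groups is compared with the local service, with adjustment for baseline predictors, "to delineate the effect of both SC interventions within YESS".

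**The concern.** An outcome can estimate the effect of a treatment only if it is measured after the treatment has been given. The protocol sets the booklet and the 4-week assessment at the same visit, with the assessment first, and then analyses that assessment as if the booklet had come earlier.

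Two results would suffer. In the randomised comparison, a chance difference at 4 weeks could be reported as an early effect of the booklet, and a null could be read as evidence that it has no early effect. Neither reading would be valid. In the comparison with the local service, both arms have so far received one and the same service, so two contrasts by arm estimate the same quantity twice, each with less precision. That comparison is not peripheral: the effectiveness of the colocated service is the first primary aim under Study aims, and Trial design assigns it to the observational comparison with local services.

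**Working it through.** **1. The plan's own figures.** Sample size gives 1040 smokers, so 520 per arm at 1:1. I assume two-sided 5%, in keeping with the planned 95% intervals. Power = Φ[(δ − 1.96·SE0)/SE1], where SE0 uses the pooled proportion and SE1 the two separate ones.

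- 41% v 51%: SE0 = √(2 × 0.46 × 0.54/520) = 0.0309; SE1 = √((0.41 × 0.59 + 0.51 × 0.49)/520) = 0.0308; power 90.0% (stated 90%).
- 41% v 49.6%: power 79.6% (stated 80%).
- Monthly relapse: ln(53/15)/11 = 0.1147 (stated 11.5%). Three-month rate: 0.53 × (1 − 0.115)² = 41.5% (stated 41%).

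These reproduce. They concern 3 months and do not bear on the point.

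**2. Order of events.**

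| Step | Source | Difference between arms |
|---|---|---|
| Screening visit, first support session | All eligible smokers | None |
| Randomisation, before the 4-week follow-up | Randomisation | Allocation only |
| Support to 4 weeks | All eligible smokers | None |
| 4-week visit: smoking status, consent, data | All eligible smokers; Blinding | None in treatment; practitioner knew the allocation in the first five rounds |
| Envelope opened, treatment by group | Blinding; All eligible smokers | Booklet or blank |
| 3 and 12 months | Primary and secondary outcomes | Booklet already delivered |

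The 4-week measures fall in the row before the first difference in treatment. Table 1 fits this: response efficacy, perceived risk and cancer worry are first collected at 4 weeks, so those values can serve only as the starting point for later change.

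**3. What a 4-week contrast between arms would return.** The expected booklet effect is 0, so a two-sided 5% test rejects 5% of the time, by chance alone. With the 53% one-month quit rate cited under Sample size and 520 per arm, SE(difference) = √(2 × 0.53 × 0.47/520) = 0.0310, and the 95% interval is ±1.96 × 0.0310, about ±6.1 points, around a quantity that carries no information on the booklet.

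**4. Precision in the community comparison.** SE of the YESS rate at 53%:

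- one arm: √(0.53 × 0.47/520) = 0.0219, or 2.2 points;
- both arms: √(0.53 × 0.47/1040) = 0.0155, or 1.5 points.

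The YESS-community difference has SE = √(SE²(YESS) + SE²(community)). The community sample size is not given, so the gain from pooling lies somewhere between none (small community sample) and a factor of √2 (very large one).

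**5. Who belongs in that comparison.** Secondary outcomes defines 4-week cessation in everyone who agreed to support from the practitioner. Non-participants shows that some of these people do not consent to the trial. Consent is confirmed at the visit where the outcome is measured, so a comparison limited to the 1040 enrolled would condition on attending and consenting at that moment, which may be related to having quit.

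**The case against.** The strongest reply is that 4-week cessation is already framed as an outcome of the service, since its stated population is all smokers agreeing to support and not the randomised arms, and that a separate analysis plan may handle the 4-week data. The first part stands as a reading of Secondary outcomes and supports the fix. It does not remove the conflict: the general rule under Statistical analyses covers secondary outcomes without exception, and the community comparison names both arms and both interventions. The second part does not help, because these analyses are stated in the protocol and not left open.

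It is also fair to say that the order of data collection before envelope is explicit only after the first five rounds. For the earlier rounds the protocol says that practitioners knew the allocation, and does not say when the booklet was shown relative to data collection. All eligible smokers still starts allocated treatment at that visit, and a booklet handed over then cannot have caused abstinence in the preceding weeks. Knowledge of allocation could still have affected who consented and how answers were recorded. The protocol already plans a sensitivity analysis for this period (n=94).

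A reader might go further and attach a family-wise error rate to the 4-week tests. The documents do not support one: they do not enumerate such tests, the planned output is in terms of abstinence proportions, and the measures concerned are plainly correlated.

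**Conclusion.** The point holds. As written, the plan includes a 4-week contrast between arms that cannot measure the booklet, and a community comparison whose stated purpose a 4-week outcome cannot serve. Any 4-week difference between arms reflects chance or, in the first five rounds, selective consent or differential recording.

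The reach is limited. A reader might infer that the trial's main result is compromised. It is not: the primary outcome is at 3 months, the sample size rests on it, the economic analysis uses 12-month quit rates, and both time points follow the booklet. A reader might also take the fall from 2.2 to 1.5 points as the gain in the community comparison. It is the gain for the YESS rate alone, assuming 53% quitting and 520 per arm.

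This should be corrected before analysis, because it touches the first primary aim and the reading of secondary results, but it does not threaten the randomised primary comparison.

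**What to change.** 1. **Statistical analyses:** state that the 4-week measures are pre-booklet for the randomised comparison, and estimate the booklet's effect at 3 and 12 months only. If 4-week values are shown by arm, present them descriptively, with a note that differences reflect chance or, in the first five rounds, selective consent or differential recording.
2. **Comparative measurement (analysis part):** replace the comparison by arm with one comparison of the colocated service with the local service, and delete the purpose of separating both interventions.
3. **Population for that comparison:** use the one under Secondary outcomes, that is all eligible smokers who agreed to see the practitioner, including those who did not consent to the trial where their 4-week status is available. All eligible smokers already provides for asking consent to telephone contact at 4 weeks. Report how many lack a 4-week status.

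The cost is protocol and analysis-plan wording. No new data are needed and the trial's sample size does not change.

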## Introduction

Lung cancer is the third most common cancer and has the highest mortality of all cancers in the UK.^1^ It becomes more common as socioeconomic deprivation levels increase,^2^ reflecting higher smoking rates.^3^ A reduction in both all-cause and lung cancer specific mortality was reported by the US National Lung Screening Trial in 2011^4^; subsequently lung cancer screening (LCS) was adopted across North America having been recommended by the US Preventive Services Task Force in 2013.^5^ Mortality benefits of low-dose CT (LDCT) screening for LCS have subsequently been demonstrated by the Multicentric Italian Lung Detection (MILD) trial^6^ and confirmed by preliminary results from the NELSON study.^7^

More than 85% of cases of lung cancer are caused by tobacco smoking,^8^ and stopping smoking at any age significantly reduces lung cancer risk.^9 10^ LCS may provide a teachable moment for smoking cessation (SC);^9^ patients undertaking routine or acute visits to healthcare providers are more likely to be receptive to offers of help to quit.^11^

Several large studies have measured SC outcomes in the context of LCS, with results varying between higher quit rates,^12^ no difference^13^ or lower quit rates in screened versus unscreened participants.^14^ Despite the potential for important health gains, there is limited evidence on how best to integrate effective SC services in an LCS context, though lessons may be learnt from SC interventions delivered in other settings.

Evidence suggests that provision of SC support as an opt-out default generates more quit attempts,^15–17^ and higher uptake within an LCS setting.^18^ A 2014 systematic review showed benefit of materials tailored to the characteristics of individual smokers,^19^ although the included studies were conducted predominantly in the general population, rather than screening participants. Further, a recent UK study has demonstrated the efficacy of including risk information personalised to pre-existing health conditions and consequences of continuing to smoke when inviting participants to SC services.^20^ LDCT screening commonly detects smoking-related comorbidities, a consequence of participants’ long smoking histories.^21 22^ The screening process is a unique opportunity for a personalised SC intervention using these findings to improve quit rates.^23^

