### Study aims

The primary aims of the study are to:

Assess the uptake and effectiveness of a colocated opt-out SC intervention, delivered in line with National Health Service (NHS) standard best practice (SBP) guidance, as part of an LCS programme.Assess the efficacy of a personalised, theory-grounded SC intervention, incorporating participant heart and lung scan images alongside an explanation of the clinical importance of the findings and scripted communication to enhance personal salience, self-efficacy and response efficacy.

The secondary aims of the study are:

Conduct a process evaluation of both the colocated and personalised SC intervention to support interpretation of study findings.Conduct a health economic evaluation to assess the cost-effectiveness of the colocated service plus personalised feedback intervention over and above the colocated service plus SBP.

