### Trial design

This is a pragmatic, parallel-group, open, randomised controlled trial comparing an enhanced, personalised SC support package, tailored to include results from LCS, delivered in addition to an SBP cessation package, versus SBP package alone. Further, we will also compare the effectiveness of the colocated service with local stop smoking services (SSS) in an observational design.

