### Exclusion criteria

Any individual who does not have an LDCT scan, or is unable to provide informed consent.

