#### Comparative measurement in those smokers attending community stop smoking services

Anonymised data will be provided for those aged 55–80 years for dates corresponding to the study period from the local NHSSSS to compare quit outcomes in those receiving SC support through YESS with those accessing community services.

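### The 4-week comparison with community stop smoking services estimates lung screening plus the colocated service, so it should not be presented as the effect of the cessation service alone

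*Protocol article*

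**What the plan says.** Study aims (protocol article) lists as a primary aim: "Assess the uptake and effectiveness of a colocated opt-out SC intervention", delivered within a lung screening programme. Trial design says the study will "compare the effectiveness of the colocated service with local stop smoking services (SSS) in an observational design".

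The analysis section on community stop smoking services (under Statistical analyses) takes 4-week cessation, compares the intervention and SBP groups with local service users aged 55–80 over the same period, and gives the purpose as "to delineate the effect of both SC interventions within YESS". The model is logistic regression, "adjusting for observed baseline differences in predictors of cessation including age, gender, heaviness of smoking and level of education". The word 'including' leaves the covariate list open.

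The two sides are selected differently:

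- **YESS.** Exclusion criteria removes "Any individual who does not have an LDCT scan". Participants and recruitment requires the USPSTF, PLCO or LLP criteria to be met before a scan is offered. SC provision (All eligible smokers) places the visit about 4 weeks after screening, "and hence after scan results have been issued by YLST".
- **Comparator.** The data-source section of the same title says: "Anonymised data will be provided for those aged 55–80 years", from the local service for the study dates. It sets no screening or lung-cancer-risk criterion.

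The Introduction calls screening a possible teachable moment. It reports that earlier studies found higher quit rates, no difference, or "lower quit rates in screened versus unscreened participants".

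**The concern.** The stated purpose attributes the difference between YESS and community smokers to the cessation interventions. The two groups also differ in having been scanned and told the result, which the protocol itself says may change quitting. An effect of the scan, in either direction, would be carried into the estimate and read as an effect of the service.

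The comparison bears on a primary aim. A colocated service no better than the community one could look effective because the scan prompted quitting. A useful one could look ineffective because a reassuring scan reduced quitting. Nothing in the article limits the interpretation to the package of screening plus service.

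**Working it through.** **1. What the model can identify.** Let G = 1 for YESS and 0 for the community, S = 1 if scanned, and X the covariates:

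logit P(quit) = a + b_service·G + b_scan·S + c·X.

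Exclusion criteria fixes S = 1 whenever G = 1. If the comparator is unscreened, S = G and the model becomes a + (b_service + b_scan)·G + c·X. Only the sum can be estimated. A design matrix holding both G and S, an intercept and four covariates has rank 6 with 7 columns. Adding covariates to X, here or in an SAP, does not change this.

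**2. Simulation of the planned adjustment.** The settings are all assumptions: true service OR 1, 1040 smokers per side, 300 replicates, invented covariate distributions and effects, and adjustment for age, gender, heaviness of smoking and education.

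| Assumed screening OR | Adjusted 'service' OR | Declared significant |
|---|---|---|
| 0.67 | 0.67 | about 100% |
| 0.80 | 0.80 | 69% |
| 1.00 | 1.00 | 5% |
| 1.25 | 1.26 | 72% |
| 1.50 | 1.49 | about 100% |

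The adjusted estimate returns the screening OR.

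**3. Size on the risk scale.** The article states no sample size or power for this comparison, so there is no figure of the plan to reproduce. For a base rate I use the 53% one-month quit rate that Sample size cites for NHS services. Its odds are 0.53/0.47 = 1.128.

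- Screening OR 1.3: odds 1.466, rate 1.466/2.466 = 59.4%, or +6.4 points.
- Screening OR 1/1.3: odds 0.867, rate 0.867/1.867 = 46.5%, or −6.5 points.
- With base rates of 35% to 45%, the shift at these ORs is still about 6 points.

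**4. Chance of a spurious finding.** Two-sided 5% test, SE = √[p1(1−p1)/n1 + p0(1−p0)/n2], with p0 = 0.53 and assumed community sizes n2. For OR 1.3, n1 = 1040 and n2 = 1000, SE = 0.0219, z = 0.0645/0.0219 = 2.94, and the rejection probability is about 84%.

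| YESS n1 | Screening OR | n2 = 500 | n2 = 1000 | n2 = 2000 |
|---|---|---|---|---|
| 1040 (arms pooled) | 1.3 or 1/1.3 | 67% | 84% | 93% |
| 1040 (arms pooled) | 1.15 or 1/1.15 | 25% | 35% | 45% |
| 520 (one arm) | 1.3 or 1/1.3 | 55% | 68% | 76% |

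**5. Referrals.** SC provision allows some YLST smokers to be passed to the same local service. Suppose a share f of the comparator had been scanned with the same screening OR. The spurious difference at OR 1.3 would then shrink to (1 − f) × 6.4 points: 5.8 at f = 10% and 5.1 at f = 20%. Both shares are assumptions, as the article gives none. Because the data are anonymised, S may not be known in the comparator, so these referrals dilute the contrast without making the scan effect separable.

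**The case against.** The strongest reply is that the package is the intended target. Study aims places the colocated service inside a screening programme, colocation in the screening van cannot exist without screening, and Trial design calls the comparison observational. On that reading nothing is misattributed. This stands as a fair reading of the aim. It does not rescue the analysis wording, which assigns the contrast to the cessation interventions and says nothing about screening. If the package is meant, saying so is the correction.

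A reader might go further in four ways that the documents do not support:

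- **That no comparator smoker was scanned.** The referral route in SC provision means some may have been. The comparator's screening status is not stated, and 'mostly unscreened' is an inference.
- **That covariate adjustment is useless.** Age and heaviness of smoking plausibly capture part of the lung-cancer-risk selection, and the list is open. Only the scan itself is beyond adjustment.
- **That the service is bound to be flattered.** The Introduction reports results in both directions and also no difference, in which case this bias would be nil.
- **That age is the only filter on the comparator.** It is also limited to the local service and the study dates, though neither addresses screening or risk.

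It is also fair to say that the magnitudes are illustrative. The screening ORs and community sizes are assumed, and separate comparisons of each arm give lower probabilities than the pooled one.

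**Conclusion.** The point holds as one of attribution. Screening is almost completely aliased with YESS membership, so the planned contrast cannot isolate the effect of the cessation service, and no covariate left to an SAP can change that. With a null service and an assumed screening OR of 1.3 either way, the spurious difference is about 6 points from a 53% base rate. It would be significant in roughly 55% to 93% of cases, depending on whether arms are pooled and on a community sample of 500 to 2000. At an OR of 1.15 with arms pooled the range is 25% to 45%. These figures assume a wholly unscreened comparator and a two-sided 5% test. The direction is unknown.

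A reader might infer that the trial's main result is compromised. It is not: both randomised arms are scanned, so the 3-month primary comparison is untouched. The correction should be made because this contrast serves a primary aim and the wording decides what may be concluded from it.

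**What to change.** In the analysis section on community services, replace the stated purpose with wording such as: this observational comparison estimates the combined effect of lung screening and the colocated service against community support largely without screening, and will not be attributed to the cessation service alone. Align the sentence in Trial design.

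Ask the local service to exclude or flag smokers referred from YLST, where they can be identified.

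Two additions are optional. The first is to restrict the comparator to the range of age and heaviness of smoking that overlaps with YESS, as far as the service data allow. The second is to report the screening OR at which the conclusion would change. This adds no trial information, but it shows how robust the reading is.

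The cost is a few lines of text and possibly one extra item in a data request already planned. The downside is a narrower claim and perhaps a slightly smaller comparator. The change does not answer whether to colocate a service or refer screened smokers to the community, which would need a comparison among screened smokers.
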